1. STILL AWAY
2. <2 WEEKS
3. 2-4 WEEKS
4. >4 WEEKS
5. DON’T KNOW
6. How many nights did (NAME) spend away during this most recent trip?

*L: [NAME] ne oduogo ka oa e woudhe manonindoe oko mogik karang’o*

*S: Ni usiku ngapi [NAME] amechukua akiwa kwa safari yake ya mwisho*

Number________

(Don’t know=-1)

1. Was the most recent overnight trip outside of “Rachuonyo”?

*L: Otieno adi mane [NAME] onindoe oko e woudhe mogik?*

*S: Safari yako ya mwisho ilikuwa nje ya “Rachuonyo”?*

1. YES
2. NO
3. DON’T KNOW
4. In which district/s did (NAME) spend the most time during this most recent overnight trip?

*L: E distrikt mane ma [NAME] ne okawo thuolo mang’eny ewuoth mane onondo oko mogikni?*

*S: Ni wilaya ipi aliweza kukaa sana katika safari yake?*

District (drop down, including Don’t know) (skip to 24)

1. In which EA within Rachuonyo did (NAME) spend the most time during this most recent overnight trip?

*L: En EA mane ei Rachuonyo ma [NAME] yandeonindoe ahinya e woudhe maoko mogik?*

*S: Katika wilaya “EA” ipi [NAME] amechua muda mrefu katika safari yake ya mwisho katika wilaya ya Rachuonyo?*

EA _________/Don’t know

1. What was the main reason for making this most recent overnight trip?

*L: Ang’o momiyo ne odhi e wuodhe mogik ni?*

*S: Kwa nini alienda kwenye safari hii?*

1. WORK/LOOKING FOR WORK
2. BUYING/SELLING AT MARKET
3. ATTENDING SCHOOL OR UNIVERSITY
4. VISITING RELATIVES OR FRIENDS
5. FUNERAL
6. OTHER (SPECIFY) __________________
7. Did (NAME) make any other trips outside “EA name” in the last3 months?

*L: Bende [NAME] ne odhi wuoth moko oko mar “nying EA” e dweche 3 mokalo?*

*S: [NAME] amekuwa na safari nje ya nje “ Jina la EA” kwa muda wa miezi 3 zilisopita?*

1. YES
2. NO
3. DON’T KNOW
4. When did (NAME) come back from his/her most recent overnight trip?

*L: E wuodhe mogik [NAME] nodwogo kara ng’o?*

*S: [NAME] Alirudi lini kutoka safari yake ya mwisho*

1. STILL AWAY
2. <2 WEEKS
3. 2-4 WEEKS
4. >4 WEEKS
5. DON’T KNOW
6. How many nights did (NAME) spend away during this most recent trip?

*L: [NAME] ne oduogo ka oa e woudhe manonindoe oko mogik karang’o*

*S: Ni usiku ngapi [NAME] amechukua akiwa kwa safari yake ya mwisho*

Number________

(Don’t know=-1)

1. Was the most recent overnight trip outside of “Rachuonyo?

*L: Otieno adi mane [NAME] onindoe oko e woudhe mogik?*

*S: Safari yako ya mwisho ilikuwa nje ya “Rachuonyo?*

1. YES
2. NO
3. DON’T KNOW
4. In which district/s did (NAME) spend the most time during this most recent overnight trip?

*L: E distrikt mane ma [NAME] ne okawo thuolo mang’eny ewuoth mane onondo oko mogikni?*

*S: Ni wilaya ipi aliweza kukaa sana katika safari yake?*

District (drop down, including Don’t know) (skip to 24)

1. In which EA within “Rachuonyo did (NAME) spend the most time during this most recent overnight trip?

*L: En EA mane ei “Rachuonyo ma [NAME] yandeonindoe ahinya e woudhe maoko mogik?*

*S: Katika wilaya “EA” ipi [NAME] amechua muda mrefu katika safari yake ya mwisho katika wilaya ya“Rachuonyo*

EA _________/Don’t know

1. What was the main reason for making this most recent overnight trip?

*L: Ang’o momiyo ne odhi e wuodhe mogik ni?*

*S: Kwa nini alienda kwenye safari hii?*

1. WORK/LOOKING FOR WORK
2. BUYING/SELLING AT MARKET
3. ATTENDING SCHOOL OR UNIVERSITY
4. VISITING RELATIVES OR FRIENDS
5. FUNERAL
6. OTHER (SPECIFY) __________________
7. Are there any other persons who live in this house that we have not listed?

*L: Bendo nitiere ji mamoko manindo e odini mapodi ok andiko nying gi?*

*S: Kuna watu wengine wanaoishi kwenye nyumba hii ambao hatuna majina yao?*

1. YES (Go back to QUESTION 1 and fill out this form for that person)
2. NO
3. Are there any other people who may not be members of your family, such as domestic servants, lodgers or friends who usually live here?

*L: Bende nitiere ji mamoko ma ok jodala ka mapile, kaka jotich, wede, kata osiepe ma mane onindo ka otieno manyoro?*

*S: Kuna watu wengine wanaoishi kwenye nyumba hii kama marafiki, wafanyi kazi au watu wanaolipia malazi yao ambao hatuna majina yao?*

1. YES (Go back to person questionnaire start)
2. NO (Go to results page).

**Part IV-Malaria/Anaemia-Record the RDT result and anaemia result for each person**

**Person ID: _________________________**

1. Temperature:______________
2. Blood sample taken?
   1. YES
   2. NO, REASON NOT TAKEN
      1. REFUSED
      2. NOT PRESENT
      3. OTHER___________
3. RDT Result
   1. POSITIVE
   2. NEGATIVE
   3. INVALID
   4. NOT DONE , SPECIFY REASON____________

**If RDT positive, only offer treatment if the person is not pregnant* ***OR*** *has not been diagnosed with malaria and taken antimalarials in the past 2 weeks*

1. Hemocue reading___________________

**If HB is less than or equal to 110 treat with iron, if below 60 refer for immediate medical care*

1. Blood smear prepared?

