## b. Study site and population.

Ethnicity in Rachuonyo is predominantly of the Luo ethnic group. Local residents depend upon farming and cattle and goat herding for subsistence. Compounds are distributed broadly across a rolling landscape intersected with small streams and rivers. The main malaria vectors in the area are *Anopheles gambiae*, *An. arabiensis*, and *An. funestus*. Malaria transmission is seasonal, with two seasonal peaks in malaria cases reflecting the bimodal rainfall pattern, with the heaviest rainfall typically occurring between April and June, with a smaller peak between October and November each year. Most malaria is caused by *Plasmodium falciparum*. Community surveys that were conducted in 2010 indicated parasite prevalences averaging 14.8% but ranging from 0% to 51.5%. School surveys that were conducted in the same year at indicated an average parasite prevalence of 25.8% (range 0 to 71.4%).

Detailed cross-sectional surveys have been conducted in an area of 100km^2^ (5x20km) in Rachuonyo district to determine small-scale variations in malaria transmission intensity. (see figure 1). This area was sub-divided into 400 500m^2^ areas referred to as cells.

[figure not shown]

*Figure 1. The Rectangle indicates the area (5*20km) in Rachuonyo district where the activities will take place. Each dot is an individual household. White dots indicate the parasite prevalence in school surveys in the area in the year 2010; colour intensity indicates variation in the altitude. The proposed study area lies at an altitude of 1400-1550 meters.*

All structures in this 5 x 20km area were geo-located by remote sensing and 3,200 compounds were randomly selected for detailed characterization of malaria exposure. After informed consent, household characteristics were recorded for all houses that belonged to the selected compound. Temperatures were taken from each permanent resident of the selected compounds and individuals were asked to provide a single finger-prick blood sample for detection of malaria parasites by PCR [15], malaria-specific antibody responses by ELISA [[12](#_ENREF_12)] and haemoglobin concentration by HemoCue photometer [Angelholm, Sweden]. Febrile individuals were screened in the field using rapid-diagnostic tests [Paracheck, Orchid Biomedical Systems, India] and treated with first line artemisinin-combination therapy.

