Blood samples will be collected from all individuals aged between 6 months and 20 years. Blood will be collected by fingerprick and used to test for malaria by rapid diagnostic test (Premier Medical First Response Combo^®^,HRP-2 & LDH based), for determination of haemoglobin levels using a Copack Colour Scale ® (Oststeinbek, Germany), to prepare a microscopy slide and to collect blood into an EDTA microtainer tube and onto a filter paper. RDTs will be used for clinical decision-making; slides will read after the campaign to determine the relative sensitivity of RDTs and PCR in the study setting. The Copack Haemoglobin Colour Scale system has been available since 2001 and is a reliable and validated method to assess haemoglobin levels. The test consists of a drop of blood being placed on the test strip, and after 30 seconds is compared to the hue on the provided colour scale. The gradient of the colour scale indicates whether and how severely anaemic a person is with the scale ranging from <4 to 14 g/dl of haemoglobin. The collected blood samples will be analysed for parasite prevalence by microscopy PCR and the detection of malaria-specific antibody responses by ELISA (see section g: laboratory analyses).

Screening the non-sentinel group

In addition to testing the sentinel age-group, all other individuals aged above 20 years will have their temperature by ear thermometer and blood samples taken by fingerprick. Those that are febrile (as defined by the range of the specific thermometer used) will be tested for malaria using RDTs otherwise blood will be collected as described above for the same purposes.

Using the sentinel population to detect microscopic and submicroscopic parasite carriers

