Each occupied house in the randomly selected compounds will be visited by a team of fieldworkers. The head of the house will then be interviewed using a personalized digital assistant (PDA) to record information. The interview will assess household construction, wealth indices and use of anti-malarial measures (recent IRS activities, bednet ownership and use, use of mosquito coils, sprays etc.). Each selected participant or their parent/guardian will be interviewed inquiring about recent fever episodes, treatment seeking behaviour, ITN use and travel history. The transcript of the questionnaire is given in Appendix E. On the PDA translations for questions will be available by pressing buttons for DhoLuo or Kiswahili. The questionnaire it will be broken down into 4 parts; the first records details of the household, the second logs bednets, the third records personal details and the last records results of tests completed.

Temperature will be measured by ear thermometer; a single fingerprick blood sample will be used to i) determine haemoglobin levels using a Copack Haemoglobin Colour Scale system (blood sample spotted onto a special filter paper), ii) prepare a microscopy slide (sample taken directly from the finger onto a slide) and iii) collect a blood sample into an EDTA microtainer tube and onto a filter paper for parasite PCR and the detection of malaria-specific antibody responses by ELISA. For all individuals with fever (≥37.5°C), the presence of malaria parasites will be determined immediately by rapid diagnostic test (RDT, directly from the finger). Anyone with fever and a positive RDT will be treated for malaria at the home according to national guidelines (see above for procedures women of childbearing age). All participants will be told their haemoglobin level immediately, and any person found to be anaemic will be provided haematinics according to national guidelines. The volume of the blood sample taken for all measurements combined will be 200-300μL.

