**10. DATA MANAGEMENT:**

a. Data storage

All data from the questionnaires during cross-sectional surveys will be collected on PDAs and downloaded each evening into Microsoft Access. Paper records will be used as a back-up to the PDAs for recording visited households and RDT and anaemia results. All consents, assents, PDAs and computers to which data are downloaded will be locked so that only the principal investigators and data management staff will have access to the data. Data will be cleaned on an on-going basis.

b. Data analysis

To assess the impact of the intervention, methods appropriate for cluster-randomized trials will be used [30]. The primary outcome will be PCR-confirmed parasitaemia. The prevalence by PCR in each cluster will be calculated and the unadjusted risk ratio (RR), or mean difference between clusters will be calculated. An overall estimate of programme impact will be obtained, and 95% confidence intervals will be adjusted for observed between-cluster variance. Formal hypothesis testing will be undertaken using stratified unpaired t-tests. Adjustment for covariates will be undertaken replacing the cluster means and proportions with covariate-adjusted residuals from regression analysis of individual-level data.

One of the key outcomes of the study is the community-wide effect of hotspot targeted interventions. To address the question of the distance over which this community-wide effect exists, we will relate parasite prevalence and antibody prevalence to the distance from the centre of the hotspot in intervention and control clusters.

Additionally, the analysis adjusts for baseline characteristics on malaria infection, haemoglobin concentration and socio-economic status. Statistical analysis will be carried out using STATA^®^ software, version 10.0. (Stata Corporation, Texas, USA).

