**16. BUDGET JUSTIFICATION**

**Personnel salaries and benefits.** Funds included here include salary cover for the period of the intervention and follow-up studies (including preparation and analysis) for all Kisumu-based staff. Staff include the study coordinator, clinical officer, data specialist, administrative and logistical support, entomology supervisor and technicians, laboratory technologists and community health workers.

Costs are broken down in to **intervention costs** and **survey costs.** Under each intervention field workers, equipment, supplies and any drugs or insecticides required are given. These encompass the following costs as detailed below:

Field workers This includes all salaries for casual staff during the particular study, such as community health workers and guides.

**Equipment, supplies, drugs/insecticides**. This is estimated to include sprayers, COPACK haemoglobin kits, nets and small laboratory equipment including thermometers, scissors, staining jars etc. Supplies covers the estimated cost of all the non-field work supplies required for the study. It includes photocopying, stationary, communication and printing over the study period. Drugs/insecticides covers costs of RDTs, Coartem, SP+AQ and ferrous sulphate sufficient to treat the estimated number of surveyed individuals for each stage as well as the insecticides required for IRS and larviciding.

**Travel and transportation**. This includes local travel and international travel of LSHTM staff to Kenya. All local travel costs during survey preparation and implementation are included. All costs for local travel and accommodation have been estimated using standard KEMRI mileage and per diem charges.

**Laboratory costs** This covers the costs of processing all blood samples collected for PCR and serological analyses.

Note: some **contingency costs** are included in this budget; additional contingency funds are available through wider Malaria Transmission Consortium budgets. Institutional overheads are levied at 15%.

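### The survey form asks for a HemoCue reading and prints unitless limits of 110 and 60, while the surveys use a colour scale in g/dl: device, unit and limits need reconciling

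*Protocol*

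**What the plan says.** **Survey procedure.** Section 9g (Procedures: evaluation phase) uses one fingerprick sample to "determine haemoglobin levels using a Copack Haemoglobin Colour Scale system". For the questionnaire it points to the appendix: "The transcript of the questionnaire is given in Appendix E".

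**Range and unit of that device.** Section 9f, on screening the sentinel group, describes the same Copack system, "with the scale ranging from <4 to 14 g/dl of haemoglobin".

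**Budget.** Section 16 lists "COPACK haemoglobin kits" among the equipment.

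**Survey form.** Appendix E, Part IV labels the field "Hemocue reading" and adds the instruction "If HB is less than or equal to 110 treat with iron, if below 60 refer for immediate medical care". Neither the field nor the limits carry a unit.

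**Where HemoCue otherwise appears.** Section 9b reports that the earlier survey of the study area measured "haemoglobin concentration by HemoCue photometer". The form line may have been carried over from that survey, but the protocol does not say so.

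**Other text on acting on haemoglobin.** Sections 9f and 9g refer anaemia treatment to national guidelines, and section 12d promises treatment for low haemoglobin. None of them gives a number or mentions referral for low haemoglobin.

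**Analysis.** Section 10b states that "the analysis adjusts for baseline characteristics on malaria infection, haemoglobin concentration and socio-economic status".

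**The concern.** The body of the protocol and the form it cites disagree on the device, and their numbers are of different magnitude. In the document at hand, the form is the only place with numeric haemoglobin limits and the only place with a referral trigger for low haemoglobin, so a reader cannot correct it from the main text. Appendix E is headed as a transcript of the PDA screens, and participants are told their level on the spot. The text therefore appears to be what field staff would act on.

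Two things are at stake. The first is care: without a unit, one team may convert the reading and another may not, and the iron and referral rules are then applied differently. The second is data: one field could hold values such as 11 and 110 for the same haemoglobin level, and haemoglobin is named as an adjustment variable.

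**Working it through.** No sample size or power figure is involved. The check sets the range of the device against the limits on the form, then counts the measurements concerned.

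**Inputs**
- Colour scale: below 4 to 14 g/dl (section 9f); same system named for the surveys (section 9g).
- Form limits: at or below 110, and below 60, no unit (Appendix E, Part IV).
- Clusters: up to 16 (section 9a).
- Evaluation zone sample per cluster: 100 to 500 (section 9e); planning figure 300.
- Hotspot sample per cluster: at least 50 (section 9e), up to 100 (section 9g); planning figure 100.
- Surveys: six (section 9g).

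**Step 1: values entered as read, in g/dl.** The highest scale value is 14, and 14 < 60 < 110. Every possible reading meets both conditions, so the form cannot tell an anaemic from a non-anaemic participant.

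**Step 2: limits assumed to be in g/L.** With 1 g/dl = 10 g/L:
- 110 g/L ÷ 10 = 11.0 g/dl
- 60 g/L ÷ 10 = 6.0 g/dl
- top of the scale: 14 g/dl × 10 = 140 g/L

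Both limits then lie inside the range of the scale and would discriminate. This is a unit conversion only. It does not say that these are the right limits.

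**Step 3: which reading does the protocol support?** Neither is stated. The form prints no unit, and no section gives a conversion or tells staff to make one.

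**Step 4: measurements concerned, at 16 clusters.**

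| Basis | Per survey | Over six surveys |
| --- | --- | --- |
| Lower bounds | 16 × (100 + 50) = 2,400 | 14,400 |
| Planning figures | 16 × (300 + 100) = 6,400 | 38,400 |
| Upper bounds | 16 × (500 + 100) = 9,600 | 57,600 |

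These are measurements, not distinct people. With fewer than 16 clusters the counts fall in proportion, at 150 to 600 per cluster per survey.

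**Step 5: the covariate.** Section 10b does not name the source of baseline haemoglobin. Section 11 calls the March 2012 survey the baseline, whereas section 9c uses the same word for the earlier survey, which used HemoCue. If the March 2012 form is the source, a consistent tenfold difference in unit would only rescale the regression coefficient and leave the adjusted comparison unchanged. Harm needs mixed units within the field.

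**The case against.** The strongest reply is that experienced staff would recognise 110 and 60 as g/L, and that read this way the rule works. On this view the defect is a wrong device label and a missing unit in an appendix, while the body text already sends anaemia treatment to national guidelines. Much of this stands, and it rules out three stronger claims that a reader might infer.

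- **That every participant would be referred.** This follows only if g/dl values are entered and compared literally. It shows that the form fails as printed, and does not predict what field teams would do.
- **That 38,400 people are affected.** This is the planning-figure count multiplied over six surveys. It counts contacts rather than people, and section 9e says the actual numbers depend on hotspot and zone size.
- **That the adjusted analysis is corrupted.** The protocol does not tie the covariate to this field, and nothing shows that units would in fact be mixed. Section 10b also plans an unadjusted risk ratio or difference, which haemoglobin does not enter.

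What the reply does not remove is the contradiction on the device. Nor does the reference to national guidelines supply the missing unit, or any referral rule that could replace the one on the form.

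**Conclusion.** The inconsistency is real and should be corrected. The form names a different device from the survey procedure, and its limits cannot be applied to the colour scale in g/dl without a conversion that the protocol does not give. The consequence that the documents support is a possibility: inconsistent use of the iron and referral triggers, and haemoglobin recorded in mixed units. An effect on the baseline adjustment depends on two further conditions, that this field is the source and that units are mixed within it.

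The mismatch concerns 2,400 to 9,600 measurements per survey, assuming the maximum of 16 clusters and the protocol's own sampling bounds. That the limits are in g/L is an assumption. The primary PCR outcome, the sample size and the unadjusted comparison are not affected. The point merits attention because it touches the only numeric haemoglobin limits in the protocol and costs almost nothing to put right.

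**What to change.** Reconcile sections 9f and 9g with Appendix E, Part IV:

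1. Name one haemoglobin device for the surveys, in the procedures and on the form alike.
2. Print the reading field and both action limits in that device's unit.
3. Have the clinical team confirm the limits, including that the chosen device can be read at them. No limit is proposed here.
4. In section 10b, add one sentence naming the survey, device and unit from which baseline haemoglobin is taken.

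A PDA check that rejects values outside the device's range would help but is optional. The cost is one edit to the PDA form and its paper back-up, plus one sentence in the protocol. No procedure, sample or visit is added.

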   1. YES
   2. NO, REASON_____________

Record barcode number and date on blood slide

1. Filter paper blood spots prepared?
   1. YES
   2. NO, REASON_____________

Record barcode number and date on filter paper

1. Whole blood collected?
   1. YES
   2. NO, REASON_____________
2. Record Barcode number and date on microcontainer

Barcode Number: ________________________**Appendix F: Side effects monitoring form form insecticides**

Ask the head of house whether anyone in the house has suffered from the following symptoms since we sprayed the house/issued bednets

Area (Cell)_____________

Compound/house code_______________

| **Questions** | | | **Response (Y/N/DK)** |
| --- | --- | --- | --- |
| **ENGLISH** (Since we carried out IRS/gave bednets have you had…….. | **LUO** (Nyaka wa kir yath/chiw nede, be isebdo gi….. | **KISWAHILI** (Tangu tunyunyize dawa/gawa neti, je umehisi…… |  |
| **1.Headache** | Wich bar | Kuumwa na kichwa |  |
| **2. Itching/or rash** | Guonyruok/guonyo | Kuwashwa ama harara |  |
| **3. Difficulty in breathing** | Pek mar yueyo | Ugumu wa kupumua |  |
| **4.Dizziness** | Kawirawira | Kusinziasinzia |  |
| **5. Vomiting/nausea** | Ng’ok/chuny lep | Kutapika ama kuchafukwa na moyo |  |
| **6. Stomachache** | Ich kach | Kuumwa na tumbo |  |
| **7.Others/specify** | Mamoko/wachi | Mengineyo/fafanua |  |

If Y is answered to any of the above ask the head of the house which person/s suffered these symptoms and then call up each participant and complete the adverse reporting form. If serious also complete the serious adverse event form.

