*Indoor residual spraying*

The insecticide that will be used for IRS will be decided on following consultations with DOMC and will be one of the following: lambdacyhalothrin, alphacypermethrin or deltamethrin. Activities and actual spraying will be undertaken by study personnel; IRS will be timed before the peak transmission season in March, at the time-point that is deemed most efficacious by comprehensive malaria transmission models [19] and again after 6 months.

Heads of compounds will be visited by the study team and consent sought. Compounds where the head, or someone with the authority to provide consent, is absent will be visited for a maximum of three times to maximize IRS-coverage in the hotspots. The study team will remove all movable items from the structures that will be sprayed. Any large items that cannot be removed will be moved into the centre of the room and covered with plastic sheets. Sprayers will use protective clothing, masks and gloves and will dispense the insecticide using a back pack sprayer. The walls and roof of all structures in the compound (residential and non-residential) will be sprayed for at least 15 minutes according to guidelines for the insecticide used. The structures will be left locked for 2 hours after which the doors and windows will be opened and allowed to air out for 30 minutes. After this the head of the house may enter to sweep clean. During the government-led IRS program of 2011 lambda-cyhalothrin was used and was reported to occasionally result in itching. Approximately 1 week after the spray households will be revisited to interview members on any reported side effects (see appendix F& H).

Spraying will be repeated at 6-monthly intervals (visits 1 and 3).

*Long-lasting insecticide treated nets distribution*

At the point of the census study staff will document the number of sleeping spaces within each house. At the time of the intervention (March 2012), the study team will distribute one LLIN for each sleeping space within the house, hang the net and explain the proper use and maintenance of the net. All study nets will be labelled for later identification. To avoid potential irritation to the insecticide used in the LLIN, nets will be hung outside for at least 24 hours before being distributed to communities to allow the strength of the insecticide to wane.

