**Appendix G: Adverse reporting monitoring form for FSAT**

Call up each participant treated, **one by one**.

Area (Cell)_____________

Compound/house code_______________

Participant’s ID,.

Partcipant Name______________

Year of birth_________________

Sex _________M/F

Ask the participant about how they took AL:

- - 1. What time did you take your Coartem last night?

*S: Je ulimeza (dawa ya malaria) coartem saa ngapi jana usiku?*

*L: Ni mwonyo coartem (yadh malaria) saa adi otieno manyoro?*

________________

- - 1. How did you take the drugs?

*S: Ulimezaje hizi madawa?*

*L: Nimwonyo yadhgi nade?*

________________

- - 1. Did you take the drugs with any food/fluids?

*S: Je ulimeaza madawa na chakula au kinyuaji chochote?*

*L: Be nimwonyo yath gi chiemo kata math moramora?*

________________

Then ask the participant the following questions e.g. “In the last 24 hours have you had a Headache?” Write down the answer in the relevant column, like this: put a (**Y**) for “Yes”, a (**N**) for “No” and a “**DK**“ for “Don’t know”. Continue with the next problem and record the answers until all have been asked about. For an adverse event (i.e. where Y is recorded)., document each event on the following adverse reporting form. If any event is termed as severe/life threatening complete the second serious adverse event reporting form as well.

Below are the questions translated into Luo, and Kiswahili.

| **Questions** | | | **(Y/N/DK)** |
| --- | --- | --- | --- |
| **ENGLISH** (In the last 24hrs have you had…….. | **LUO** (Kuom seche piero ariyo gi ang’wen mokalo, be isebdo gi….. | **KISWAHILI** (Kwa masaa ishirini na manne yaliyopita,je umehisi…… |  |
| **1.Headache** | Wich bar | Kuumwa na kichwa |  |
| **2. Itching/or rash** | Guonyruok/guonyo | Kuwashwa ama harara |  |
| **3. Difficulty in breathing** | Pek mar yueyo | Ugumu wa kupumua |  |
| **4.Fatigue/body weakness** | Jony mar del | Uchovu ama unyonge wa mwili |  |
| **5.Dizziness** | Kawirawira | Kusinziasinzia |  |
| **6. Muscular pain** | Rem mar leche | Maumivu ya misuli |  |
| **7. Joint pains** | Rem mar fuonde | Maumivu ya viungo |  |
| **8. Vomiting/nausea** | Ng’ok/chuny lep | Kutapika ama kuchafukwa na moyo |  |
| **9. Fever** | Liet mar del | Joto jingi |  |
| **10. Stomachache** | Ich kach | Kuumwa na tumbo |  |
| **11.Others/specify** | Mamoko/wachi | Mengineyo/fafanua |  |

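### Appendix F sets a house-level question but scripts an individual one, so spray and net side effects in members other than the head may go unrecorded

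*Protocol*

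**What the plan says.** Appendix F has three parts.

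- **Instruction line.** "Ask the head of house whether anyone in the house has suffered from the following symptoms since we sprayed the house/issued bednets". The respondent is the head; the subject is every member of the house.
- **Stem above the symptom list.** In English, "Since we carried out IRS/gave bednets have you had"; in Luo, "Nyaka wa kir yath/chiw nede, be isebdo gi"; in Kiswahili, "Tangu tunyunyize dawa/gawa neti, je umehisi". Each listed symptom has a single Y/N/DK answer, and the form is identified by cell and compound or house code.
- **Follow-up.** "If Y is answered to any of the above ask the head of the house which person/s suffered these symptoms". Each person named is then called up for the adverse event form, and for the serious adverse event form where it applies.

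Appendix G, the corresponding form for screening and treatment (FSAT), works person by person. It begins "Call up each participant treated" and uses the stem "In the last 24hrs have you had".

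Section 9f, under indoor residual spraying, says that about one week after spraying "households will be revisited to interview members on any reported side effects", and refers to Appendices F and H. Section 12c undertakes to document reported side effects of all the interventions by questionnaire.

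**The concern.** The instruction and the follow-up in Appendix F are about the house. The stem between them is worded for one person. If the stem is what gets asked, a head who has had no symptoms can truthfully answer no to every line, and the form then gives no route to anyone else. The adverse event and serious adverse event forms in Appendix H are completed for spraying and nets only after a yes, so an omission at this step carries through to them.

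What is at stake is how completely harms of spraying and nets are recorded. Section 9f itself notes that the insecticide used in the 2011 government programme occasionally caused itching, so a non-zero rate of reactions is expected. Fieldworkers who read the script and fieldworkers who follow the instruction would also collect different information on the same form, and the literal reading errs towards under-reporting.

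**Working it through.** No calculation applies, because the point concerns the wording of a form. The check is a comparison of texts.

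1. **Whom does the form mean to cover?** The instruction asks about anyone in the house, and the follow-up asks the head which person or persons were affected. Both make sense only if the answer is for the whole house. That is the intended scope.

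2. **Whom does the stem address?** The English stem addresses the respondent, as does the Appendix G stem "In the last 24hrs have you had". The Luo and Kiswahili stems in Appendix F close with the same words as their counterparts in Appendix G. In Appendix G those words are correct, because participants are called up one at a time. In Appendix F they are put to the head about a whole house.

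3. **What follows from each answer?**

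| How the fieldworker asks | Head well, another member affected | Result |
| --- | --- | --- |
| Follows the instruction line | Head reports the other member, if aware of the symptom | Y; the member is called up |
| Reads the stem as printed and the head answers for himself or herself | Head answers no | N; nobody is called up |

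The form has no later step at which another member is asked directly.

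4. **Are children provided for?** Part III of the Appendix E questionnaire directs questions about children to the primary caretaker. Appendix F has no such direction.

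5. **Can the loss be sized?** Three quantities would be needed: how often the stem is read literally, the number of people per house, and the risk of a symptom per person. The protocol gives none of them. The sample size section implies 100/35 = 2.9 and 50/9 = 5.6 people per compound, but sections 9b and 9g make clear that a compound can contain several houses, and Appendix F is completed by house. No figure is given for the risk of a reaction. The direction of the error is clear; its size is not.

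**The case against.** The strongest reply is that the form states its household scope twice, before and after the stem, and that nothing in the protocol orders the stem to be read word for word in place of the instruction. A trained fieldworker would probably ask about the house. This stands, and it is why the point is a risk and not a demonstrated loss.

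Nor does the form of address settle the matter. Some household items in Appendix E, such as those on cooking fuel and toilet type, also use the singular in Kiswahili. The mismatch rests on the conflict with the form's own instruction and on the match with Appendix G.

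Section 9f is not clearly in conflict either. Interviewing members about reported side effects fits a two-step form in which the head reports and the affected members are then seen. Asking the head on behalf of the house is a common field choice and is not in itself an error.

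There is also a partial safety net. Section 11 places FSAT and net distribution at the same time, and Appendix G asks each treated person about itching or rash and difficulty in breathing. It reaches only those given treatment, asks about the last 24 hours, and section 11 puts spraying after the FSAT and net roll-out, so it does not replace Appendix F.

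A reader might infer more than this: that reactions in other members are in fact missed, that a head-only answer captures just one event in every three to six, or that those missed are the people most exposed. The protocol supports none of these. The first ignores the instruction line. The second applies people per compound to houses and assumes that every fieldworker reads the script literally. For the third, nothing says that other members are more exposed than the head.

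**Conclusion.** Appendix F is internally inconsistent: a house-level instruction and follow-up surround an individual-level stem in all three languages. Because members are called up only after a yes from the head, a literal reading may leave side effects of spraying and nets unrecorded in other members, including children.

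The conclusion assumes only that some fieldworkers will use the printed question as printed. The size of any under-recording cannot be estimated from the protocol. Side effects are not among the stated objectives or outcomes, and the primary outcome, sample size and main analysis are untouched. This is a modest defect in a working safety form, worth correcting because the correction is specific and nearly free.

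**What to change.** Reword the stem in English, Luo and Kiswahili to match the instruction, for example: *Since we sprayed / gave nets, has anyone living in this house, including children, had …*. Ideally the question is put to the head with the other members present, and the caretaker answers for young children. Check the two translations by the back-translation already planned for the consent forms.

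No new field is needed for a denominator. The Appendix C census lists residents by house and should be used for any person-level rate.

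The cost is rewording one stem in three languages and a few more minutes per house at a visit already planned.
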